### **Follow up of (Serious) Adverse Events**

Participants who experience adverse events will be retained in the study. A follow-up of SAE will be organized accordingly, under the supervision of the sponsor, depending on the type of event. Patients with SAE will be followed until resolution or stabilization of the effect will be noted.

### **Notification of safety and protective measures (see ClinO, Art 62, b)**

If immediate safety and protective measures have to be taken during the conduct of the study, the investigator notifies the Ethics committee of these measures, and of the circumstances

[figure not shown]

necessitating them, within 7 days.

### **6.3 (Periodic) safety reporting**

An annual safety report (ASR/DSUR) is submitted once a year to the local Ethics Committee by the Investigator (ClinO, Art. 43 Abs).

In international multicentric studies the ASR/DSUR contains information from all sites including information from sites outside of Switzerland. The Sponsor distributes the ASR/DSUR to all the participating Investigators.

### **6.4 Radiation**

N/A.

### **6.5 Amendments**

Substantial changes to the study setup and study organization, the protocol and relevant study documents are submitted to the Ethics Committee for approval before implementation. Under emergency circumstances, deviations from the protocol to protect the rights, safety and well-being of human subjects may proceed without prior approval of the Ethics Committee. Such deviations shall be documented and reported to the Ethics Committee as soon as possible.

A list of all non-substantial amendments will be submitted once a year to the competent EC together with the ASR.

### **6.6 (Premature) termination of study**

The Sponsor may terminate the study prematurely according to certain circumstances, e.g.

- Ethical concerns,
- Insufficient participant recruitment,
- When the safety of the participants is doubtful or at risk (e.g. when the benefit-risk assessment is no longer positive),
- Alterations in accepted clinical practice that make the continuation of the study unwise, or
- Early evidence of harm or benefit of the experimental intervention

Upon regular study termination, the Ethics Committee is notified via BASEC within 90 days (ClinO, Art. 38).

Upon premature study termination or study interruption, the Ethics Committee is notified via BASEC within 15 days (ClinO, Art. 38).

Health-related data at the end of the study will be coded upon end of data analysis.

## **6.7 Insurance**

In the event of study-related damage or injuries, the liability of the institution CHUV (centre hospitalier universitaire vaudois) provides compensation, except for claims that arise from misconduct or gross negligence.

# **7 FURTHER ASPECTS**

## **7.1 Overall ethical considerations**

The study design (randomized controlled trial) will permit to have a good internal validity of the study. Moreover, the CCI used as main outcome is a validated index of general postoperative morbidity and it enables to encompass all complications that a patient may present. The inclusion of several centers internationally will increase the generalizability of the results (external validity). The complication rate after PD remains high (around 60%) and malnutrition has been established as a risk factor of postoperative complication. An intervention that could improve the nutritional status of the patients might lead to a decrease of morbidity after PD.

If the results are favorable, this study will permit to establish an EEN protocol to improve patient outcomes after PD. Patients undergoing PD could rapidly benefit of this management, and EEN could become the new standard of care for the perioperative nutrition management after PD. The results of this study could be implemented and translated into daily clinical practice promptly.

The need for research in this field is clearly present, as the issue of postoperative nutrition after PD is not resolved and does not reach an overall consensus among international pancreatic surgeons. The numerous presentations, debates in congresses, and our recently published survey on that subject attest and highlight the absence of universal consensus and lack of solid data.

The results of this study would go beyond the only scientific interest, as they will directly impact patients undergoing pancreas surgery. As pancreas cancer incidence is projected to grow in the upcoming years, pancreas surgery number will correlatively increase. Ultimately, in the current era of growing health expenditures and need for cost containment, if EEN allows decreasing complications and length of stay, it could also decrease the overall costs for each patient hospitalization for PD, which could have important positive repercussions on the health care system.

Particular attention will be paid to the process of randomization in order to ensure a sound methodology.

An overall fair balance for the study participant will be maintained.

## **7.2 Risk-benefit assessment**

There are several adverse events associated with nasojejunal tube and enteral nutrition: poor

tolerance, nausea, vomiting, diarrhea, tube obstruction, or bronchial inhalation. Nursing teams are trained to use the equipment and will perform the same care as usual: position verification, flushing, nasal fixation, nasal eschar surveillance. With these measures, the risk of adverse events associated with the study is judged to be low.

From the investigators' perspective, we hypothesize that the EEN intervention will be a benefit for patients included in the study group. Benefits of EEN could be a decrease of postoperative complications and a shorter length of stay. Nevertheless, the control group cannot be considered disadvantaged as currently no intervention of this type exists in visceral surgery. It is also possible that the participation to the study will not bring any benefits.

## **8 QUALITY CONTROL AND DATA PROTECTION**

### **8.1 Quality measures**

A research nurse or collaborator will be hired for this study. He/she will have specific training in all important study-related aspects. Monitoring of the study will be performed by the clinical research center (CRC) of the CHUV.

For quality assurance the sponsor, the Ethics Committee or an independent trial monitor may visit the research sites. Direct access to the source data and all study related files is granted on such occasions. All involved parties keep the participant data strictly confidential.

### **8.2 Data recording and source data**

Study data will be recorded using electronic Case Report Form created on REDCap. This software contains among others an audit trail. Each participant will have an individual CRF. CRF will not identify patients by their name or birth date but will have a coded identification (e.g., patient 1: 23, patient 2: 14, or patient 3: 46).

The source data of this study are the original medical records of the patients containing clinical, biological, and radiological findings. All data will be recorded using eCRF documents. Standardized questionnaires (EORTC) will also be distributed to the patients and compiled.

### **8.3 Confidentiality and coding**

Trial and participant data will be handled with uttermost discretion and are only accessible to authorized personnel who require the data to fulfil their duties within the scope of the study. On the eCRFs and other study specific documents, participants are only identified by a unique participant number.

A research coordinator of our division will store in his/her office the identification list in a key-closed drawer.

[figure not shown]

Audit trail embedded in the database (REDCap) will ensure traceability according to ClinO, Art.

18. Only password-protected access will be permitted and safety backups on storage media (CHUV secure servers) will prevent misuse of recorded information.

Only non-genetic data will be used.

#### **8.4 Retention and destruction of study data and biological material**

Appropriate data archiving is the responsibility of the PI of the study. All study data are archived for 10 years after study termination or premature termination of the study in a coded manner. All the study data collected will be archived on a CHUV network storage server whose integrity, security and backups are provided by the department of informatic system (DSI).

No biological material will be conserved specifically for this study.

### **9 MONITORING AND REGISTRATION**

Monitoring activities have the purpose to ensure that the study is conducted in accordance with the clinical study protocol, applicable laws, regulations and procedures. This includes verifying the quality and integrity of data and the protection of the rights, welfare, and safety of subjects participating in the study. The CRC of the CHUV will monitor the study for the centers in Switzerland. The CRC appointed monitor will be responsible for ensuring that the activities are conducted in compliance with the ICH-GCP E6 (R2) guidelines, the Declaration of Helsinki, all applicable sponsor requirements for the study in object as well as any applicable local law and regulation. It will be the responsibility of the sponsor to ensure that all monitor working in the context of the study is adequately trained and complies to all applicable sponsor requirements. The necessary visits for the monitoring will be done following the recommendations of the monitoring committee of the CRC. Visits prior the start, in the middle, and at the end of the study will be realized. Data issued from the eCRF and the database will be monitored. The same monitoring will be applied by the centers outside of Switzerland.

The source data and documents will be accessible to monitors and potential questions will be answered during monitoring.

The present study will be registered in the Swiss National Clinical trial Portal (SNCTP via BASEC). Moreover, this trial will be registered in ClinicalTrials.gov and the protocol of this study will be published in a peer-review journal such as *Trials* or *BMJ Open*.

### **10 FUNDING / PUBLICATION / DECLARATION OF INTEREST**

Fundings of CHF 20'000 and CHF 100'000 were received from the Livio-Glauser Foundation and from the Valery Foundation for this study. Moreover, the department of Visceral Surgery will also

provide some funding.

This study should enable to publish several manuscripts in peer-reviewed journals with high impact in the surgical community. Preparation of the articles will start as soon as inclusion of all patients will be closed. The investigators declare to have no conflict of interest to disclose.

## Appendix 1: Schedule of assessments

| Study periods                            | Screening    | Entry | Intervention |          |                 | Discharge       | Follow-up |    |
|------------------------------------------|--------------|-------|--------------|----------|-----------------|-----------------|-----------|----|
| Visits                                   | 1            | 2     | Daily        |          |                 | 3               | 4         | 5  |
| Days                                     | Preoperative | -1    | 0            | 1-7      | Hospitalization | 14 ^ | 30-45     | 90 |
| Patient information and informed consent | x*           | x*    |              |          |                 |                 |           |    |
| Patient eligibility confirmation         |              | x     |              |          |                 |                 |           |    |
| Demographics                             | x            | x     |              |          |                 |                 |           |    |
| Randomization                            |              | x     |              |          |                 |                 |           |    |
| Standard surgery (not study procedure)   |              |       | x            |          |                 |                 |           |    |
| Nasogastric tube (EEN group)             |              |       | x***         |          |                 |                 |           |    |
| Physical examination                     | x            | x     | Daily        |          |                 | x               | x         |    |
| Vital signs                              | x            | x     | Daily        |          |                 | x               | x         |    |
| Metabolic tests ‡                        |              | x     |              |          | 2x/week         |                 |           |    |
| Nutrition tests Ω                        |              | x     |              |          |                 |                 | x         |    |
| Body measures°                           |              | x     |              |          |                 | x               | x         |    |
| Indirect calorimetry                     |              |       |              | on POD 5 |                 |                 |           |    |
| EORTC QLQ-C30                            | x**          | x**   |              |          |                 | x               | x         | x  |
| Subjective tolerance (VAS 0-10)          |              |       |              | x        |                 |                 |           |    |
| Complications - CCI                      |              |       |              |          |                 | x               | x         | x  |
| Complications - Clavien                  |              |       |              |          |                 | x               | x         | x  |
| LOS                                      |              |       |              |          |                 | x               |           |    |
| Readmissions                             |              |       |              |          |                 |                 |           | x  |

Demographics include the measure of serum CA 19-9 at admission in case of pancreatic cancer.

**EEN:** early enteral nutrition, **EORTC:** European Organisation for Research and Treatment of Cancer, **VAS:** Visual Analog Scale, **CCI:** Comprehensive Complication Index, **LOS:** length of stay, **POD:** postoperative day.

‡ **Metabolic tests:** CRP, procalcitonin, simple blood count, coagulation tests, electrolytes (sodium, potassium, calcium, magnesium, phosphate), creatinine, urea, blood glucose, liver and pancreatic function tests, prealbumin, albumin, triglycerides.

Ω **Nutrition tests:** folate, magnesium, iron, ferritin, transferrin saturation, vitamin D, calcium, phosphate and parathormone, vitamin E, HbA1c (glycated hemoglobin).

° **Body measures:** lean body mass using bioelectrical impedance analysis and strength using handgrip.

\* Filled either during screening visit or at hospital admission.

\*\* The preoperative EORTC questionnaire will be filled during screening visit or on hospital entry day. In total, four questionnaires will be filled. The last one on postoperative day 90 will be filled by the study nurse who will perform the phone call.

\*\*\* At the end of surgery and in the EEN study group only: polyurethane single or double lumen feeding nasogastric tube (Freka®) 8F.

^ Discharge on day 14: current mean hospital stay.

[figure not shown]

**Service de chirurgie viscérale**

[name], Chef de Service

[name]

[name]

A maximum of six months is permitted between the screening and the intervention. If the interval is longer, a new (more recent) consent form will be signed.

The calorimetry should ideally be performed between POD 3 and POD 7. The accepted period to perform the calorimetry taking into account the clinical variability is between POD 3 and POD 30.

The visit n°4 should ideally be performed between POD 30 and POD 45. The accepted period to do the visit n°4 taking into account the clinical variability is between POD 20 and POD 60.

The visit n°5 should ideally be performed on POD 90. The accepted period to do the visit n°5 taking into account the clinical variability is between POD 75 and POD 115.

The most important questionnaire is the questionnaire of the visit n°5 on POD 90. If this questionnaire is not performed, it will be considered a deviation to the protocol. Absence of other questionnaires will not be considered as protocol deviation.

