| Endpoints    | 
1. Primary outcome: postoperative morbidity, as evaluated according to the CCI within 90 postoperative days.
 
2. Secondary endpoints:
 
 
• Major postoperative complications, as evaluated according to the Clavien classification within 90 postoperative days (Clavien grade >II).
 
• Specific complications after PD will be recorded:             
 
○ Surgical site infections (SSI)
 
○ Postoperative pancreatic fistula (POPF)
 
○ Delayed gastric emptying (DGE)
 
○ Postpancreatectomy hemorrhage (PPH)
 
○ Biliary fistula
 
○ Gastrojejunal anastomosis fistula
 
○ Pancreatitis
 
 
 
• Length of stay will be quantified from operative day until discharge.
 
• Readmissions will be assessed from day 1 after discharge until postoperative day 90.
 
• Patients quality of life (QoL) will be assessed by the EORTC (European Organisation for Research and Treatment of Cancer) QLQ-C30 questionnaire.
 
• Metabolic response to EEN will be assessed with biological measurements preoperatively and twice weekly during hospital stay (currently already measured according to our PD care map):             
 
○ C-Reactive Protein (CRP) and procalcitonin
 
○ Simple blood count, coagulation tests
 
○ Electrolytes: sodium, potassium, calcium, magnesium, phosphate
 
○ Creatinine, urea, blood glucose, liver and pancreatic function tests, prealbumin, albumin, triglycerides
 
 
 
• Assessment of malabsorption due to PD with biological measurements preoperatively and between the 4th and 6th postoperative week:             
 
○ Folate, iron, ferritin, transferrin saturation
 
○ Vitamin D, parathormone, vitamin E
 
○ Glycated hemoglobin (HbA1c)
 
 
 
• Measure of lean body mass using bioelectrical impedance analysis and of muscle strength based on the handgrip preoperatively, on discharge day, and on the first follow-up visit.
 
• Measure of resting energy expenditure using indirect calorimetry on postoperative day 5.
 
 |

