### 3.2 Primary and secondary endpoints

The primary endpoint measuring postoperative morbidity will be assessed using the CCI within 90 postoperative days.

Secondary endpoints are the following:

- Most severe postoperative complications will be measured using the Clavien classification within 90 postoperative days.
- Specific complications of PD will be recorded:
  - SSI, further divided into 'superficial', 'deep' and 'organ-space' according to the specific anatomic involvement and the Centers for Disease Prevention definition.
  - POPF are classified into three grades, A, B and C, according to the consensus of the International Study Group for Pancreatic Surgery (ISGPS).
  - DGE, which is classified into three grades, A, B and C, according to the consensus of the ISGPS.
  - PPH, which is also classified into three grades, A, B and C, according to the consensus of the ISGPS.
  - Biliary fistula (no standard definition)
  - Gastrojejunal anastomosis fistula (no standard definition)
  - Pancreatitis (no standard definition)
- Length of stay will be measured from operative day until discharge.
- Readmissions will be counted until postoperative day 90.
- Patients' QoL will be assessed by the EORTC (European Organisation for Research and Treatment of Cancer) QLQ-C30 questionnaire. This questionnaire will be filled 4 times: at preoperative consultation or admission, at patient's discharge, between the 4th and 6th postoperative week and on POD 90 (via phone call).
- The subjective tolerance of EEN will be assessed daily during the first 7 postoperative days, using a visual analogue scale (0-10). Objective tolerance will be assessed by the amount of EEN as a percentage (tolerated/total amount of EEN required).
- Time required (in days) to reach respectively 50% and 100% of the daily caloric targets required (30 kcal/kg/day if BMI <30 kg/m^2 and 25 kcal/kg/day if BMI ≥30 kg/m^2, protein target: 1.5 g/kg/day).
- Metabolic response to EEN will be assessed with biological measurements preoperatively and twice weekly (currently already measured, according to our PD care map):
  - C-Reactive Protein (CRP) and procalcitonin
  - Simple blood count, coagulation
  - Electrolytes: sodium, potassium, calcium, magnesium, phosphate
  - Creatinine, urea, blood glucose, liver and pancreatic function tests, prealbumin,

[figure not shown]

albumin, triglycerides

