- Various malabsorption due to PD surgery: measurements will be made twice, once before surgery and once between the 4th and 6th postoperative week during the follow-up visit. As PD might induce duodenal and pancreatic insufficiencies postoperatively due to the resection of the duodenum and the pancreatic head, it is presently unknown if EEN might have an effect on these insufficiencies by improving the overall nutritional state and the mucosal trophicity of the small bowels.
  - Duodenal insufficiency: folate, magnesium, calcium, iron, ferritin, transferrin saturation
  - Exocrine pancreatic insufficiency: malabsorption of fat soluble vitamins: vitamin D (with calcium/phosphate balance and parathormone) and vitamin E
  - Endocrine pancreatic insufficiency: due to risk of developing a secondary diabetes, HbA1c (glycated hemoglobin) will be measured.
- Body measure using bioelectrical impedance analysis (BIA) and muscle strength using handgrip will be measured preoperatively, on discharge day, and on the first follow-up visit.
- Resting energy expenditure will be measured on POD 5 using indirect calorimetry.

Each of these endpoints will be measured in the study (EEN) and control (oral nutrition) groups.

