#### **4.3 Study procedures**

Given the rate of annual procedures, a recruitment of about 60% of eligible patients, and based NUTRIWHI Trial  
Version 5.0, 20/10/2023

[figure not shown]

on the experience of two randomized studies successfully completed in the Visceral Surgery Department (NCT0508300, NCT00512213), the planned overall study duration is three years including the recruitment period and follow-up. For patients the study duration will be from enrolment until POD 90, date of last follow-up phone call. The expected hospitalization duration for each patient will be approximately 14 days, which is the current mean hospital stay after PD in our department.

Eligibility of the patients will be confirmed on the day before the operation (day -1). Then, patients will be randomized before the operation (day -1) in either the control arm or the experimental one (EEN).

Standardized surgical procedure in all eligible patients: In terms of surgical details, all patients will receive a prophylactic dose of antibiotics (cefuroxime) 30 minutes before incision and first have exploratory laparotomy followed by conventional or pylorus-preserving PD. Pancreaticojejunostomy will be performed. End-to-side hepaticojejunostomy will be performed with single-layer interrupted sutures. A gastrojejunostomy will finally be constructed. Two perianastomotic drains will be placed.

Specific study procedure: At the end of surgery (after the three anastomoses are finished but before closure of the abdomen) and in the EEN study group only, a polyurethane single or double lumen feeding nasojejunal tube (Freka®) 8F will be inserted by the anesthesiologist and placed under direct palpation and visual control by the surgeon, 30 cm distally to the gastrojejunostomy into the jejunum. The tube will be attached according to current practice to the nose wing with a tape. The patient will therefore be under general anesthesia during tube insertion and no x-ray control will be needed.

Postoperatively, patients will receive standardized perioperative care according to the ERAS protocol in both arms.

From a nutritional point of view, this includes:

- The day before surgery: 2 carbohydrate drinks of 200 ml
- The operative day: 2 carbohydrate drinks of 200 ml up to 2 hours preoperatively, then postoperative free drinks
- On postoperative day (POD) 1: bouillons, creams, yogurts, drinks  $\geq 2l$
- On POD 2: light diet, drinks  $\geq 2l$
- On POD 3: normal diet (half portion)

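### The last outcome visit is accepted from POD 75, but CCI, Clavien grade and readmissions run to POD 90, and no later check is required after an early call

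*Protocol*

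**What the plan says.** Section 3.2 gives the primary endpoint a fixed horizon: "The primary endpoint measuring postoperative morbidity will be assessed using the CCI within 90 postoperative days". Clavien grade has the same 90-day limit. For readmissions the section says: "Readmissions will be counted until postoperative day 90". The synopsis agrees: "Readmissions will be assessed from day 1 after discharge until postoperative day 90".

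The Appendix 1 table schedules CCI and Clavien grade at visits 3 (discharge), 4 and 5, and readmissions at visit 5 only. Section 4.3 makes that visit the end of participation: "For patients the study duration will be from enrolment until POD 90, date of last follow-up phone call".

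The notes below the table set the tolerance. The target is clear: "The visit n°5 should ideally be performed on POD 90". The accepted range is wider: "The accepted period to do the visit n°5 taking into account the clinical variability is between POD 75 and POD 115". The same notes accept visit 4 from POD 20 to POD 60. The only lapse at visit 5 that they call a deviation is a missing questionnaire.

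A similar mismatch affects a secondary endpoint. Section 3.2 says: "Resting energy expenditure will be measured on POD 5 using indirect calorimetry". The notes name POD 3 to 7 as ideal, then add: "The accepted period to perform the calorimetry taking into account the clinical variability is between POD 3 and POD 30".

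**The concern.** A visit tolerance is harmless when the outcome can still be recovered in full at either end of it. That is true of a call after POD 90, because a patient contacted on POD 100 can report everything up to POD 90. It is not true of a call before POD 90, because the remaining days have not yet happened. A patient called on POD 75 meets the protocol, has had the last planned contact, and has up to 15 days of the primary endpoint still to run.

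Complications and readmissions in those days may go unrecorded, and the patient's 90-day CCI would then be too low. This cannot be left to the analysis stage, since an analysis plan cannot restore events that were never collected. Appendix 1 also conflicts with Section 4.3, which dates the last call at POD 90.

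**Working it through.** **1. The plan's own sample size.** Inputs from Section 5.1: control mean CCI 35, SD 20, 30% reduction (10.5 points), two-sided alpha 0.05, power 80%.

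- n per group = 2 × (1.960 + 0.842)² × 20² / 10.5² = 56.9, rounded up to 57.
- With 20% drop-out: 57 / 0.8 = 71.25, rounded up to 72 per group, 144 in total.

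Both figures reproduce. The visit window does not enter the calculation.

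**2. The window.**

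- Call on POD 75: 90 − 75 = 15 days unobserved; 15 / 90 = 16.7% of the horizon.
- Call on POD 89: 1 day unobserved.
- Call on POD 90 to 115: 0 days unobserved. Up to 115 − 90 = 25 later days may be reported, but the endpoint definition excludes them.

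Only the early side shortens observation. The 16.7% is a share of time, not of events.

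**3. Is there a required safety net?** The protocol does not ask for re-contact or a record check after a call on POD 75 to 89. Two other routes exist without being tied to the endpoint: medical records are the source data (Section 8.2), and SAEs go to the sponsor within 24 hours (Section 6.2).

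**4. Possible size.** The documents do not say what share of CCI burden arises on POD 76 to 90 or how many patients would be called early. Both are assumed here:

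- s = share of each arm's mean CCI, and so of the difference, arising on POD 76 to 90: 1% to 10%.
- f = share of patients called on POD 75: 10% to 50%, the same in both arms.
- Nothing after the call is captured by any other route.
- CCI is treated as divisible over time, which is a simplification.

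Observed difference d = 10.5 × (1 − s × f). Power with 57 per group = Φ(d / [20 × √(2/57)] − 1.960), where 20 × √(2/57) = 3.746.

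| s | f | d | Power |
|---|---|---|---|
| none lost | – | 10.50 | 80.0% |
| 1% | 10% | 10.49 | 80.0% |
| 5% | 25% | 10.37 | 79.0% |
| 10% | 50% | 9.97 | 75.9% |

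In the last row the control mean falls by 35 × 0.05 = 1.75 points and the EEN mean by 24.5 × 0.05 = 1.23. Most of the loss therefore cancels in the comparison: the difference shrinks by 10.5 × 0.05 = 0.53 points.

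**5. Calorimetry.** The endpoint is stated for POD 5 and accepted from POD 3 to 30, so two compliant measurements can lie 30 − 3 = 27 days apart. Section 4.3 expects a stay of about 14 days, so the later part of the range lies after the expected discharge.

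**The case against.** The strongest reply is that Appendix 1 sets a tolerance for a visit and does not redefine the endpoint, which stays at 90 days for everyone. POD 90 is the stated target, CCI and Clavien grade are also collected at visits 3 and 4, and later events may surface in the records or as SAE reports, since a hospitalization meets the SAE definition. All of this stands and limits the size of the problem. It does not close the gap. Visits 3 and 4 come before the missing days, and the protocol does not require a search of the records to POD 90. Section 4.2 says patients are usually referred from outside, so later care may plausibly take place elsewhere and not reach the centre's records.

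Three stronger readings are tempting, and the documents do not support them.

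- A reader might infer that the primary outcome is defined over different windows in different patients, and that late calls inflate CCI. The definition is the same for all and already excludes events after POD 90.
- A reader might infer bias between arms, because the trial is open-label and call timing is flexible. The window is identical in both arms, Section 5.1 says that investigators and outcome adjudicators are blinded, and nothing shows that timing would differ by arm.
- A reader might infer that late calorimetry is usually done after EEN has ended. Section 3.4 ties the end of EEN to oral intake and gives no expected duration.

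**Conclusion.** The point holds in a limited form. A compliant visit 5 on POD 75 to 89 leaves 1 to 15 of the 90 days without scheduled ascertainment of CCI, Clavien grade and readmissions, and no later check is required. Readmissions are the most exposed, because visit 5 is their only scheduled collection.

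The effect on the result is unknown and probably small. If early calls are equally common in both arms, the main consequence is a lower recorded CCI level, with perhaps a slight dilution of the difference. The 75.9% power figure rests on pessimistic assumed inputs and on no other capture of late events; it is an illustration, not an estimate. The change is still worth making, because the loss affects the primary outcome, cannot be repaired afterwards and costs little to prevent.

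The calorimetry mismatch is a secondary matter of reconciling the stated day with the accepted range.

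**What to change.** - In the Appendix 1 notes, set the accepted window for the visit 5 outcome assessment to POD 90 to 115. Alternatively, keep the present tolerance and require a second call or a record check to POD 90 for anyone contacted earlier. A second call is the safer of the two where later care may have been given elsewhere.
- State that only complications and readmissions with onset by POD 90 count, and record onset dates. The endpoint definition already implies this, so the sentence only makes it explicit.
- Reconcile Section 4.3, which dates the last call at POD 90, with the window in Appendix 1.
- Reconcile the POD 5 calorimetry endpoint in the synopsis and Section 3.2 with the accepted range in Appendix 1.

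The cost is a few lines of text, plus a repeat call or record check for any patient already contacted before POD 90. The documents do not say how many there are. The total of 144 patients is unchanged.
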